# Interdisciplinary Rehabilitation for Concussion Recovery (i-RECOveR): protocol of an investigator-blinded, randomised, case series with multiple baseline design to evaluate the feasibility and preliminary efficacy of a 12-week treatment for persistent post-concussion symptoms

**DOI:** 10.1186/s40814-022-01153-6

**Published:** 2022-09-05

**Keywords:** Concussion, Mild traumatic brain injury, Interdisciplinary, Rehabilitation

## Abstract

**Background:**

Up to 25% of concussed individuals experience persistent post-concussion symptoms (PPCSs) which may interfere with the return to pre-injury activities and cause significant stress. Given that multiple etiological factors are thought to contribute to PPCSs, an interdisciplinary approach is recommended. This pilot study aims to primarily investigate the feasibility of a novel interdisciplinary treatment for PPCSs. Given this intervention is novel, uncertainty exists in terms of potential recruitment and retention rates, adverse events, and treatment adherence and fidelity. These factors will be explored to inform the feasibility of a phase-2 randomised controlled trial. Preliminary efficacy of this intervention will also be explored.

**Methods:**

Fifteen individuals with mild traumatic brain injury and PPCSs will receive up to 12 weeks of interdisciplinary treatments including psychology, physiotherapy, and medical interventions. Primary feasibility outcomes including data on recruitment and retention rates and treatment adherence will be explored descriptively. The cognitive therapy rating scale will be used to assess treatment fidelity. A single-case series with multiple baseline design will be used to explore preliminary efficacy. Participants will be randomly assigned to baseline phases of 2, 4, or 6 weeks. Regarding patient-centred secondary outcomes, the Rivermead Post-Concussion Symptoms Questionnaire will be assessed three times a week during baseline and treatment phases. Secondary outcomes also include measures of mood, sleep and fatigue, physical functioning, return to activity, and health-related quality of life. Patient-centred outcomes will be assessed at baseline, pretreatment, post-treatment, and one- and three-month follow-up. Thematic analysis of participant experiences will be explored through qualitative interviews.

**Discussion:**

Results from this trial will inform the feasibility and preliminary efficacy of this interdisciplinary concussion intervention and whether proceeding to a future definitive phase-2 randomised controlled trial is worthwhile. Understanding the end-user perspective of the treatment will also enable modifications to the treatment protocol for future trials to best suit the needs of individuals with PPCSs after mTBI. Outcomes from this trial can be directly translated into community rehabilitation programmes.

**Trial registration:**

ANZCTR, ACTRN12620001111965. Registered 27 October 2020, https://www.anzctr.org.au/Trial/Registration/TrialReview.aspx?id=379118

**Supplementary Information:**

The online version contains supplementary material available at 10.1186/s40814-022-01153-6.

## Introduction

Concussion/mild traumatic brain injury (mTBI) is the most prevalent form of traumatic brain injury (TBI), constituting 75–90% of all TBIs [27. , 53. , 59. ], with 1.6–3.8 million sport- and recreation-related concussions occurring annually in the USA alone [53. ]. There is limited literature on the incidence of concussion in Australia, although some have estimated that 170,000 concussions are sustained annually in Australia [108. ]. Concussion is defined by the World Health Organization and the American Congress of Rehabilitation Medicine as an acute brain injury that results from biomechanical forces (i.e. linear and rotational accelerations) to the head that causes functional disturbance within the brain. Common concussion symptoms include headaches, dizziness, nausea [28. , 43. , 58. , 83. ], sleep disturbance [48. ], fatigue [74. , 75. ], forgetfulness, poor concentration [6. ], irritability, anxiety, and depression [6. ].

Biomechanical forces of linear and rotational acceleration and deceleration have been identified as mechanisms underlying concussion [87. ]. These forces shift the brain within the skull and may result in a cascade of functional disturbances [31. ], inducing vestibular, oculomotor, autonomic, cognitive, and behavioural sequelae, collectively known as post-concussion symptoms [72. ]. Concussion sequelae are highly heterogeneous across individuals and may result in varying functional impairment and trajectories of recovery [20. ].

In adults, post-concussion symptoms generally resolve within 7–10 days [63. , 74. ]; however, up to 25% of concussed individuals experience delayed recovery which may interfere with the return to pre-injury activities (e.g. work, education, sport) and cause significant stress for months and sometimes years after injury [1. , 16. , 17. , 38. , 82. , 88. ]. Persistent post-concussion symptoms (PPCSs) have been described as the persistence of symptoms beyond the expected timeframe of recovery (i.e. > 4 weeks; [35. ]). PPCSs are thought to reflect a range of factors beyond the original injury to the brain including stress and anxiety [14. , 96. , 98. ] and physical factors such as concomitant injury to the neck and visual and/or balance systems [44. , 61. ]. Predictors of PPCS include premorbid factors such as previous loss of consciousness (LOC) and pre-injury psychological problems [76. ], with the latter often identified as the strongest predictor of outcome [80. , 107. , 111. ]. The presence of anxiety and depressive symptoms post-concussion is associated with the persistence of concussion symptoms more generally [39. , 74. , 75. , 114. ], as are coping styles, stress levels, and expectations of poor recovery [71. , 112. ]. Being a student, female sex, and older age and being injured in a motor vehicle accident have also been associated with poor recovery [23. , 77. , 98. ].

Research into treatments for PPCSs has primarily focussed on single discipline treatments targeting a single proposed mechanism (e.g. psychological, autonomic, vestibular). Psychoeducation interventions alone demonstrate limited efficacy in reducing concussion symptoms [106. ] and therefore may not be a panacea for concussion [97. ]. Given anxiety has been implicated in the maintenance of PPCSs, psychological interventions such as cognitive-behavioural therapy (CBT) represent a promising approach for the management of PPCSs [8. ]. Individualised CBT programmes for PPCSs have demonstrated efficacy in improving psychological distress [78. , 90. ] and quality of life [47. ] and reducing PPCSs [90. , 99. ]. Physiotherapy treatments including manual therapy (e.g. manipulation or stabilisation of the neck using hands rather than machines) [32. , 41. , 84. , 110. ], vestibular rehabilitation [9. , 36. , 37. , 94. ], oculomotor system interventions [19. , 91. , 92. ], and sub-symptom exercise therapy [30. , 54. , 55. ] have demonstrated efficacy in reducing impairment in their respective domains. In addition to psychological and physiotherapy management post-concussion, medical management may also be indicated [119. ], including prescribing pharmacology for the management of concussion sequelae such as post-traumatic headache [24. , 51. ].

Although there is evidence to support the efficacy of individual interventions in reducing PPCSs, accessing single-profession treatment is potentially limiting given that multiple etiological factors are often contributing to persisting post-concussion symptoms. It contrasts with clinical guidelines which emphasise a multidisciplinary approach to concussion management [26. , 60. , 61. ]. Specialised concussion services generally include a range of disciplines, primarily neuropsychology, physiotherapy, and medicine [3. , 4. , 119. ]. There is some evidence supporting the efficacy of multidisciplinary care models for PPCSs in military personnel [15. ] and adolescent [3. , 62. ] samples. There is also some evidence supporting interdisciplinary treatment of PPCSs in civilian adults [89. ]. Using a randomised clinical trial, Rytter et al. [89. ] demonstrated that a 22-week interdisciplinary programme with modules of psychoeducation and return to work delivered by a team comprised of neuropsychologists and physiotherapists and resulted in reductions in PPCSs immediately after treatment, with the maintenance of gains demonstrated at 6-month follow-up. They also found that reduction in PPCSs correlated with improved social functioning, increased activity and life satisfaction, and reduction in fatigue [89. ]. These findings demonstrate the potential utility of a collaborative and coordinated team-based approach to concussion management. Almost 20% of participants in this trial, however, were lost to follow-up and resulted in missing data for post-treatment and follow-up assessments [89. ]. This finding raises important practical concerns with regard to recruitment and the potential difficulty of retaining participants in a randomised treatment trial.

It is clear that further scientifically rigorous work in this area is warranted to evaluate the feasibility and efficacy of interdisciplinary interventions, evaluate dosage, and identify factors that contribute to the effectiveness of such interventions. There is also a need to control for the effects of spontaneous recovery when evaluating the potential efficacy of treatments for concussion. Research trials may address this by establishing baseline rates of symptoms over time before the introduction of treatments. This pilot study, using a single-case series design with multiple baselines, therefore aims to pilot and conduct a preliminary evaluation of an interdisciplinary intervention that incorporates expertise from neuropsychology, physiotherapy, and medicine to target the primary factors thought to contribute to PPCSs. Using a single-case series experimental design principally enables the examination of the appropriateness of the trial design (e.g. choice of outcome and measurement, recruitment protocol, adherence to treatment manual) to inform the design of a subsequent definitive randomised controlled trial as well as enabling the evaluation of preliminary efficacy of this novel treatment.

### Objectives

This study aims to investigate the feasibility and preliminary efficacy of interdisciplinary treatment for reducing post-concussion symptoms beyond 4-weeks post-injury. The primary objectives of the trial were as follows:To evaluate the recruitment strategy and its effectiveness and whether eligibility criteria are too broad or strictTo quantify participant retention rates post-treatment and at 1- and 3-month follow-up timepointsTo examine therapist compliance to the manualised treatment protocolTo examine if the trial and/or treatments result in adverse effects

Secondary objectives are as follows:To evaluate in a case series the preliminary efficacy of a pilot interdisciplinary intervention including neuropsychology, physiotherapy, and medical treatment in reducing post-concussion symptomsTo evaluate whether the treatment improves secondary patient-centred outcomes including goal attainment, mood, sleep and fatigue, physical functioning, return to activity, and health-related quality of lifeTo qualitatively explore the end-user perspective and acceptability of the treatment to facilitate modifications to the treatment protocol for future trials

## Methods

### Study design

The study will use a single-case series with nonconcurrent multiple baseline A-B design across subjects with 1- and 3-month follow-up post-treatment to examine treatment efficacy and maintenance of gains. The current multiple baseline design will have three tiers, with participants randomly assigned to one of three baselines (2, 4, or 6 weeks) to maximise experimental control [104. ]. The trial will be run as five three-tiered trials to enable replication of trials for the evaluation of external validity [104. ]. The risk of bias in N of 1 trials scale (ROBiNT) and the single-case reporting guideline in behavioural interventions (SCRIBE) will be used to ensure methodological rigour and reporting [102. , 103. ]. Individual and group level data from the single-case studies will be used to examine the feasibility of the intervention to inform the trial design of a phase 2 randomised controlled trial.

We will also explore participant experiences of the intervention using semi-structured interviews and analyse this data using thematic analysis.

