### Participants

Participants will be 15 individuals aged between 16 and 70 with concussion classified as having a mild traumatic brain injury — Glasgow Coma Scale (GCS) score between 13 and 15, less than 30 min of loss of consciousness, less than 24 h of post-traumatic amnesia (PTA), and have persisting post-concussion symptoms (> 3 post-concussion symptoms rated 2 or above persisting for at least 1 month) [105. ] as indicated on the Rivermead Post-Concussion Symptoms Questionnaire (RPQ). Individuals must be at least 4 weeks post-injury but less than 12 months post-injury to ensure that symptoms are current and persistent [109. ]. Participants will also have sufficient proficiency in English to participate in the research assessments and treatment.

Exclusion criteria include moderate-severe TBI as indicated by *GCS* < 13, *PTA* > 24 h, positive findings on imaging, an acute psychiatric condition requiring intervention, significant neurological history, active substance abuse, significant medical history that would prevent completion of research assessment and/or treatments, and if they are having other concurrent treatment for concussion symptoms.

Sample size was determined based on current recommendations for single-case series methodology [49. , 104. ]. For multiple baseline designs to meet evidence standards, each phase (e.g. A — baseline or B — intervention) needs to have at least five data points. Furthermore, there needs to be at least six phases (three A-B tiers) in order to provide three replications of the experimental effect. Given these design standards, which suggest sample sizes in multiples of three, 15 participants will result in five replications of the three-tiered multiple baseline design, allowing for the evaluation of external validity [104. ].

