##### Baseline phase

Once randomised and informed of length of baseline phase, participants will complete the RPQ three times a week on a Monday, Wednesday, and Friday. They will receive the RPQ as a REDCap link via email at 8:00 am and will receive a reminder email at 5:30 pm on the same day if they have not completed the RPQ. If participants do not complete the RPQ after the email reminder, they will be sent a follow-up text message reminder at 8:00 pm. If no response is made after the 8:00 pm reminder, this data point will be noted as incomplete.

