### Interdisciplinary treatment programme

The i-RECOveR treatment manual was developed by the investigators in 2020 through consultations with collaborators from the three Melbourne-based community health centres. This treatment programme includes individualised and coordinated psychology, physiotherapy, and medical interventions.

All participants will have an initial consultation with a neuropsychologist, physiotherapist, and sports medicine physician. In these consultations, the clinicians will obtain a history from the participant and, through interview, establish the participant’s presenting complaints. Following these consultations, the clinicians will meet via case conference to triage the participant’s treatment needs, establish GAS goals, and develop a treatment plan for the participant. As part of our interdisciplinary intervention, participants with PPCSs will be offered eight sessions each of psychological and physiotherapy treatment and medical management over 12 weeks as required based on the initial consultations (Fig. 2).

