#### Adapting to telehealth during the COVID-19 pandemic

Participants will be recruited during the COVID-19 pandemic. The aim is for all treatment and research assessments to be completed face to face, but given the expected interruptions due to the state of Victoria COVID-19 lockdowns, the following adaptions are designed to facilitate ongoing data collection during the pandemic. Baseline neuropsychological assessments (T1) and 1-month follow-up post-treatment interviews (T4) will be completed via videoconference (e.g. Zoom) during the lockdowns which restricts travel for non-essential reasons. Under the state of Victoria COVID-19 lockdown restrictions, individuals may leave their house to seek treatment, therefore permitting travel to complete i-RECOveR intervention sessions. Neuropsychology intervention sessions may be completed via telehealth using the videoconferencing platform Zoom. Physiotherapy and medical services will remain face to face as permitted. For all face-to-face appointments, treatments will be conducted in accordance with established COVIDSafe plans for each clinic.

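### In an affected participant the stated RPQ analysis cannot separate an expected COVID-19 lockdown change from a treatment effect, and the nonconcurrent design protects only partly, at group level

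*Protocol article*

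**What the plan says.** All references are to the protocol article.

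- **Design.** Study design states: "The study will use a single-case series with nonconcurrent multiple baseline A-B design across subjects". It has "participants randomly assigned to one of three baselines (2, 4, or 6 weeks) to maximise experimental control". It adds: "The trial will be run as five three-tiered trials to enable replication of trials". The Participants section gives the sample size on the same basis: "15 participants will result in five replications of the three-tiered multiple baseline design".
- **Setting.** All three centres are in Melbourne (Study setting).
- **Foreseen disturbance.** The section on adapting to telehealth makes its arrangements "given the expected interruptions due to the state of Victoria COVID-19 lockdowns". They concern mode of delivery: baseline neuropsychological assessments and the 1-month interviews move to videoconference, psychology sessions may do so, and physiotherapy and medical services stay face to face where permitted.
- **RPQ analysis.** Under Aim 2 of the Data analysis plan, RPQ scores are graphed and inspected for trend, level and stability. Baseline and intervention phases are then compared by Tau-U, described as controlling for baseline trend and autocorrelation, with an omnibus test from the same online calculator. Neither lockdown status nor calendar date appears in these steps.
- **Use of the result.** Under Aim 1, signs of preliminary efficacy are one of three inputs to the decision on a randomised trial, beside completion rates and adverse events.

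**The concern.** A concurrent multiple baseline deals with outside events directly. When something happens on a given date, participants still in baseline on that date show whether it moves the outcome without treatment. In a nonconcurrent series nobody else need be in baseline then, so this check is not guaranteed.

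Here the outside event is foreseen, and because all sites are in one city, participants under observation on the same date probably share it (an inference). Several RPQ items, such as sleep disturbance, fatigue, irritability, low mood and restlessness, could plausibly move with lockdown. A change in level between phases is neither a baseline trend nor autocorrelation, so what Tau-U is said to adjust for does not remove it, and on the graph it looks like a response to treatment. If lockdown lifts around the start of treatment, the participant may appear to improve. If it begins then, a real benefit may be hidden. The individual case is a main unit of inference in this design, and the efficacy reading feeds the progression decision.

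**Working it through.** **Inputs from the article.** For the RPQ, "participants will complete the RPQ three times a week on a Monday, Wednesday, and Friday". Baselines of 2, 4 and 6 weeks therefore give 3 × 2 = 6, 3 × 4 = 12 and 3 × 6 = 18 readings. Participants "will be offered eight sessions each of psychological and physiotherapy treatment and medical management over 12 weeks as required", so the treatment phase has up to 3 × 12 = 36 readings.

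**The plan's own figure.** 5 replications × 3 tiers = 15 participants, as stated. All tiers meet the stated standard that "each phase (e.g. A — baseline or B — intervention) needs to have at least five data points". There is no power calculation to reproduce.

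**Assumption.** The article gives no SD, no lockdown dates and no lockdown effect on the RPQ. The shift is taken as d = 0.5 to 1.0 within-person SD, for example 2 to 4 points with an SD of 4.

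**One participant, no treatment effect, baseline wholly inside and treatment wholly outside lockdown.** For normal, independent readings, Tau = 2Φ(d/√2) − 1:

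- d = 0.5: 2Φ(0.354) − 1 = 0.28
- d = 1.0: 2Φ(0.707) − 1 = 0.52

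The 5% critical value with 36 treatment readings is 1.96 × √((nA + 37)/(108 nA)):

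| Tier | nA | Critical Tau | Simulated P(z > 1.96), d = 0.5 | Simulated P(z > 1.96), d = 1.0 |
|---|---|---|---|---|
| 2 weeks | 6 | 1.96 × √(43/648) = 0.505 | 0.16 | 0.55 |
| 4 weeks | 12 | 1.96 × √(49/1296) = 0.381 | 0.27 | 0.80 |
| 6 weeks | 18 | 1.96 × √(55/1944) = 0.330 | 0.35 | 0.90 |

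The last two columns come from 2,000 simulated participants per cell, with independent errors and the baseline trend subtracted when its Tau exceeded 0.2. With no shift the rate was about 0.02. Mean Tau was about 0.27 at d = 0.5 and 0.51 at d = 1.0, so the trend correction does not remove the shift. With autocorrelation of 0.3, mean Tau was almost the same and the no-shift rate was about 0.06.

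**Omnibus over 15 participants.** With inverse-variance weights, each participant's weight is 108 nA/(nA + 37), that is 15.1, 26.4 and 35.3 by tier. The total is 5 × 76.9 = 384, and the omnibus critical Tau is 1.96/√384 = 0.100. One fully shifted participant at d = 1.0 moves the omnibus by 0.52 × 15.1/384 = 0.020 (2-week tier) to 0.52 × 35.3/384 = 0.048 (6-week tier). On average, reaching 0.100 needs 0.100/0.52 = 0.19 of the total weight, or about 3 of 15 participants of average weight, all shifted the same way.

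Simulation at d = 1.0 (600 runs per scenario, no treatment effect):

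| Scenario | Mean omnibus Tau | P(z > 1.96) |
|---|---|---|
| No shift | −0.01 | 0.017 |
| Boundary shift in 1 of 15 (2-week tier) | 0.01 | 0.04 |
| Boundary shift in 5 of 15 | 0.15 | 0.83 |
| One lift at a random date, entry spread over 78 weeks | 0.04 | 0.17 |
| One lift at a random date, entry spread over 26 weeks | 0.11 | 0.54 |
| Repeated on/off lockdowns, 78 weeks | about 0 | 0.09 |
| Repeated on/off lockdowns, 26 weeks | about 0 | 0.18 |

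The entry spreads and on/off pattern are assumptions. The single-lift rows show that a change need not fall on the boundary to matter, because Tau-U compares all baseline with all treatment readings.

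**Chance of coincidence.** One event falls within a week of a given participant's boundary with probability 2/78 = 0.026 over a 78-week spread. For at least 1 of 15 the probability is 1 − (1 − 0.026)^15 = 0.32, and for at least 3 it is 0.006. Over 26 weeks the three values are 2/26 = 0.077, 0.70 and 0.10.

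**The case against.** **The design does give some control.** Participants who enter on the same day in different tiers start treatment two weeks apart, so one lockdown change cannot sit on all their boundaries. Recruitment began in January 2021 and is described as ongoing in an article published in September 2022, which suggests a long spread. Onsets and lifts push in opposite directions and tend to cancel. This stands. A reader might infer that the design offers no protection against calendar events, or that replication cannot average them out. The article does not support either reading: with one 2-week participant affected, or repeated on/off lockdowns over 78 weeks, the omnibus is little disturbed.

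**The size rests on assumptions.** At 0.5 SD, Tau of 0.28 is below all three critical values. At 1.0 SD, 0.52 only just passes the 2-week value. Both suppose a complete separation of lockdown status between phases. This stands too, and the figures should be read as an illustration.

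**A condensed article may leave such checks to the full plan.** True, and silence alone would be no finding. The point is that three stated elements do not fit together: a design presented as maximising control, a disturbance expected in advance, and an analysis that cannot isolate it.

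**Efficacy is secondary and no data are lost.** Feasibility is primary, and the RPQ readings are tied to dates. This limits the weight of the point and makes the remedy cheap, but it does not remove the ambiguity in an affected case.

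**Conclusion.** The concern holds at the level of the individual participant. Where lockdown status differs between baseline and treatment, the visual analysis and Tau-U as described cannot tell the lockdown effect from the treatment effect, and the error may go in either direction. Under an assumed shift of 0.5 to 1.0 SD and complete separation of status, Tau is about 0.28 to 0.52 with no treatment effect, so a participant could fall on either side of the critical value for the tier.

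At group level the design gives partial, indirect protection. Serious distortion of the omnibus needs several participants shifted in the same direction, as might happen with clustered recruitment. It should not be concluded that the trial's efficacy reading is invalid, or that a lockdown change would generally produce a positive omnibus result. Because the article gives neither lockdown dates nor an effect on the RPQ, no single corrected figure follows. This is a worthwhile, low-cost improvement.

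**What to change.** 1. Tag each dated RPQ reading and each T1 to T4 assessment with lockdown in force (yes/no), from public dates.
2. Shade lockdown periods on every participant's graph.
3. Add a sensitivity analysis to the Aim 2 section. Repeat the individual Tau-U on readings under a single lockdown status wherever at least five points per phase remain. Repeat the omnibus without participants whose status changes near the A-B boundary, with the width of that window fixed in advance.
4. Keep all participants in the main analysis, and qualify the individual efficacy conclusion where the sensitivity result disagrees with it.

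The cost is some data preparation and a little extra analysis, with nothing further asked of participants. The limit is that some participants will have too few readings for the restricted contrast. In the 2-week tier, with six baseline readings, only 6 − 5 = 1 can be lost. A lockdown covariate is not proposed, because the plan contains no pooled regression to hold it.
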